### Endpoints

2.9

Primary endpoints are as follows: time to first flatus, time to first defecation, time to first bowel sounds, time to initiation of a liquid/semiliquid/general diet.

Secondary outcome measures are as follows: gastrointestinal symptoms, such as nausea, abdominal distention and pain, and vomiting; serum levels of hormones, including motilin, ghrelin, bradykinin, and corticotrophin-releasing hormone (CRH); and electrogastrogram.

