**Methods::**

This study is a randomized controlled clinical trial. The participants will undergo laparoscopic colorectal cancer surgery and laparoscopic total hysterectomy. The primary outcome measure will be the gastrointestinal functional evaluation index, including the time to first passage of flatus, first defecation, first normal bowel sounds, and first consumption of liquid/semigeneral diet foods. According to good clinical practice (GCP), we will evaluate the clinical efficacy and safety of Yikou-Sizi powder hot compress and objectively study the acting mechanism of ghrelin. This pilot trial will be a standard, scientific, and clinical study designed to evaluate the effect of Yikou-Sizi powder hot compress for the recovery of gastrointestinal function after surgery and determine its overall safety.

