### Sample size estimation

2.11

The sample size estimation formula is based on completely random design sample mean comparison: 

where α = 0.05 and β = 0.2, given a 2-sided test, and n represents the sample size in each group, σ represents the standard deviation, and δ represents the between-group difference with clinical significance. The time to first flatus of the 2 groups based on the preliminary tests and clinical experience is: 
[figure not shown]
1 = 75.47 hours, S1 = 39.44, 
[figure not shown]
2 = 64.29 hours, S2 = 24.96; the time to bowel sounds is: 
[figure not shown]
1 = 44.13 hours, S1 = 32.58, 
[figure not shown]
2 = 31.22 hours, S2 = 24.26. The above data were used to estimate the value of the overall parameter. Inserting the data into the PEMS 3.1 for Windows software package, the rounded sample size in each group was 77. Assuming a 15% dropout rate, the final sample size would be 90. The sample size in the groups would be 110 cases. Therefore, the number of participants who have undergone laparoscopic colorectal cancer surgery will be 220, and the number of participants for laparoscopic total hysterectomy will be 220.

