### Data collection and statistical analysis methods

2.12

The data will be collected and recorded in the CRF forms from participants via face-to-face and telephone interviews daily. The Epidata 3.1 Statistical Package was used for data entry. Two people will perform the data entry independently, and they will be trained in advance and must pass a test before they can begin recording the data. The data will then be analyzed using the Statistical Package for the Social Sciences (SPSS) software.

The data will be analyzed by an independent statistician. If the data are divided as measurement data, the mean, standard deviation (SD), minimum value, maximum value, and median will be used for comparison. Comparison among groups will be analyzed by analysis of variance (ANOVA) and pair-wise comparison, while heteroscedasticity data or abnormal distribution will be analyzed by the rank-sum test and pair-wise comparison. If the data are divided as count data, the constituent ratio and frequency will be used for comparison. Efficient comparison between groups will be analyzed by the chi-square test at an α = 0.05 given a 2-sided test.

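### Four or more primary endpoints share one undivided two-sided 0.05 with no success rule, so the trial's false-positive rate is not fixed at 5%

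*Protocol article*

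**What the plan says.** Section 2.9 (Endpoints) uses the plural: "Primary endpoints are as follows: time to first flatus, time to first defecation, time to first bowel sounds", and then "time to initiation of a liquid/semiliquid/general diet". That is four primary endpoints, or six if liquid, semiliquid and general diet are separate milestones.

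The abstract (Methods) uses the singular for the same material: "The primary outcome measure will be the gastrointestinal functional evaluation index, including the time to first passage of flatus, first defecation, first normal bowel sounds". It describes no score, weighting or other way of combining the components.

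Section 2.11 sizes the trial from a comparison of two means, "where α = 0.05 and β = 0.2, given a 2-sided test", with planning figures for two of the endpoints, flatus and bowel sounds. The resulting 110 per group is then allotted in full to each surgery type: "the number of participants who have undergone laparoscopic colorectal cancer surgery will be 220", and likewise 220 for hysterectomy.

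Section 2.12 covers measurement data, which includes the time endpoints, as follows: "Comparison among groups will be analyzed by analysis of variance (ANOVA) and pair-wise comparison", with rank-sum tests where the assumptions fail. No level is attached to that sentence. The only level in the section is in the sentence on the chi-square test: "Efficient comparison between groups will be analyzed by the chi-square test at an α = 0.05 given a 2-sided test".

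Nowhere does the article rank the primary endpoints, divide or adjust alpha, say whether one or all must succeed, or say whether the surgery types are pooled or tested separately.

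**The concern.** The article leaves open what counts as a positive trial. Someone following it could test each endpoint at 0.05 and report the primary outcome as met on the strength of whichever one is significant. Nothing in the text forbids this, and under that practice the nominal 5% does not apply to the efficacy claim.

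The gap also affects the sample size. A trial is powered for the endpoint, or set of endpoints, that decides success. Here the size rests on one of the listed endpoints without the article saying that this one is decisive. The choice therefore cannot simply be deferred to an analysis plan, because the protocol has already sized the trial on an implicit answer.

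**Working it through.** **1. Reproduce the plan's sample size (section 2.11).** Inputs: two-sided alpha 0.05, power 80%. Flatus: 75.47 h (SD 39.44) against 64.29 h (SD 24.96). Bowel sounds: 44.13 h (SD 32.58) against 31.22 h (SD 24.26).

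Formula: n per group = 2(1.960 + 0.842)²σ²/δ².

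- Bowel sounds: δ = 44.13 − 31.22 = 12.91. With the root-mean-square SD, √[(32.58² + 24.26²)/2] = 28.72, n = 78. With the average SD of 28.42, n = 77. The stated 77 reproduces.
- Flatus: δ = 75.47 − 64.29 = 11.18. With the root-mean-square SD of 33.00, n = 137; with the average SD, n = 131. Only by using the smaller SD (24.96) for both groups does flatus come near the stated figure (79).

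The sizing therefore rests on bowel sounds. Flatus, the first-listed endpoint, has about 56% power at 77 per group and 71% at 110.

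**2. Error rate if any one of four endpoints suffices.** Independent tests: 1 − 0.95⁴ = 18.5%. With a common correlation ρ between test statistics, the rate is 1 − E[{Φ((c − √ρ X)/√(1−ρ)) − Φ((−c − √ρ X)/√(1−ρ))}⁴], where c = 1.96 and X is standard normal. For two independent populations tested separately, it is 1 − (1 − rate)². For benefit only, each test has one-directional level 0.025; under independence this gives 1 − 0.975⁴ = 9.6%.

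The documents give no correlations, so ρ is assumed:

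| ρ | 4 endpoints, two-sided | 4 endpoints, false benefit | two populations, two-sided | two populations, false benefit |
|---|---|---|---|---|
| 0 | 18.5% | 9.6% | 33.7% | 18.3% |
| 0.3 | 17.4% | 8.7% | 31.8% | 16.7% |
| 0.5 | 15.6% | 7.8% | 28.7% | 15.0% |
| 0.7 | 13.0% | 6.5% | 24.4% | 12.6% |

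The benchmark is 5% for the two-sided columns and 2.5% for the benefit columns.

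**3. Diet counted as three milestones (six endpoints).** Independent: 1 − 0.95⁶ = 26.5%; at ρ = 0.7, 16.4%. For two populations: 46.0% and 30.1%.

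**4. Other success rules.** If all four must be significant, or if the index is one composite tested once, the rate is at or below 5%.

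**5. Is a repair affordable?** Pooling gives 220 per arm, and 220 × 0.85 = 187 evaluable. This assumes that the planning figures apply to both surgery types.

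- Flatus alone at two-sided 0.05: the standard error is 33.00 × √(2/187) = 3.41; 11.18/3.41 = 3.28; power = Φ(3.28 − 1.96), about 91%.
- At the strictest Holm step (0.05/4 = 0.0125): about 78% for flatus and 97% for bowel sounds.

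**The case against.** The strongest reply is that the abstract speaks of one primary outcome, and a single composite would be tested at 5%. But the article shows no rule that would turn the components into a testable index, and 2.9 lists them separately. The abstract therefore adds a contradiction and does not settle the matter.

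Two further objections limit the claim. First, the 0.05 in 2.12 is attached to the chi-square test, not to the ANOVA or rank-sum tests that the time endpoints would use. Applying it to them is an inference, though a fair one, because 2.11 uses the same level for a comparison of means. Second, pooling and multiplicity procedures are often left to an analysis plan. That covers the technical detail, but not the choice of deciding endpoint, on which the protocol's own sample size depends.

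A reader might go further and infer that the trial's false-positive rate simply is 13-19%, or that allotting a full sample to each surgery type means each will be tested, which doubles the chances. The documents support neither inference. The percentages need an any-one rule that the plan does not state. Sizing a population is not the same as testing it, and the stratified randomization in 2.5 is compatible with one pooled analysis. Nor should the two-sided rates be read as the chance of a false claim of benefit, which is about half as large.

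The pilot label carries little weight: the same article calls the sample large, plans for 80% power with 440 participants and aims to evaluate efficacy.

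**Conclusion.** The point holds in conditional form. The article does not settle whether there is one primary outcome or several, and no stated rule holds the error for the efficacy claim at 5%. If any one of four endpoints suffices, the two-sided family-wise error is about 13-19%, and about 6.5-9.6% for false benefit. If the surgery types were also tested separately, it would be about 24-34%, and about 13-18% for false benefit. These ranges assume a common correlation of 0.7 to 0 and would be higher if the diet milestones were counted separately. The missing hierarchy, the undivided alpha and the conflict between the abstract and 2.9 can be read directly from the text. The size of the inflation depends on the success rule eventually applied.

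**What to change.** - **Abstract and 2.9:** reconcile them. State whether the primary outcome is a defined composite or a list of endpoints, and whether diet is one milestone or three.
- **2.12:** make the pooled, surgery-stratified comparison confirmatory and per-surgery tests supportive. Then either name one primary endpoint and test the others in a fixed order, each at two-sided 0.05 and only while the preceding test is significant, or apply Holm over the four. State the level for the ANOVA and rank-sum tests.
- **2.11:** match the sample-size argument to that choice. If flatus leads, the stated 77 per group cannot stand as its justification (about 137 are needed), but the pooled analysis has about 91% power at 187 evaluable per arm. If bowel sounds leads, the stated figure already corresponds to it. Moving to a pooled confirmatory analysis also means rewriting the per-surgery reasoning.

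The cost is text in these sections and no extra patients. Under fixed-order testing, lower-ranked endpoints lose confirmatory status if an earlier one fails, so the order matters; defecation and diet have no planning data in the article. Under Holm, some power per endpoint is lost: flatus would have about 78% at the strictest step in the pooled analysis.

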### Safety assessments

2.10

The kidney and liver function tests and electrocardiograph will, respectively, be undertaken before and after treatment. Any adverse events will be observed and recorded in detail at any time during the treatment phase, and also the follow-up phase.

### Sample size estimation

2.11

The sample size estimation formula is based on completely random design sample mean comparison: 

where α = 0.05 and β = 0.2, given a 2-sided test, and n represents the sample size in each group, σ represents the standard deviation, and δ represents the between-group difference with clinical significance. The time to first flatus of the 2 groups based on the preliminary tests and clinical experience is: 
[figure not shown]
1 = 75.47 hours, S1 = 39.44, 
[figure not shown]
2 = 64.29 hours, S2 = 24.96; the time to bowel sounds is: 
[figure not shown]
1 = 44.13 hours, S1 = 32.58, 
[figure not shown]
2 = 31.22 hours, S2 = 24.26. The above data were used to estimate the value of the overall parameter. Inserting the data into the PEMS 3.1 for Windows software package, the rounded sample size in each group was 77. Assuming a 15% dropout rate, the final sample size would be 90. The sample size in the groups would be 110 cases. Therefore, the number of participants who have undergone laparoscopic colorectal cancer surgery will be 220, and the number of participants for laparoscopic total hysterectomy will be 220.

### Data collection and statistical analysis methods

2.12

The data will be collected and recorded in the CRF forms from participants via face-to-face and telephone interviews daily. The Epidata 3.1 Statistical Package was used for data entry. Two people will perform the data entry independently, and they will be trained in advance and must pass a test before they can begin recording the data. The data will then be analyzed using the Statistical Package for the Social Sciences (SPSS) software.

The data will be analyzed by an independent statistician. If the data are divided as measurement data, the mean, standard deviation (SD), minimum value, maximum value, and median will be used for comparison. Comparison among groups will be analyzed by analysis of variance (ANOVA) and pair-wise comparison, while heteroscedasticity data or abnormal distribution will be analyzed by the rank-sum test and pair-wise comparison. If the data are divided as count data, the constituent ratio and frequency will be used for comparison. Efficient comparison between groups will be analyzed by the chi-square test at an α = 0.05 given a 2-sided test.

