### Trial procedure

2.5

The entire trial includes a preoperative assessment, an intervention phase (generally 7 days), and a 3-month follow-up phase. The included subjects will be randomized to the Yikou-Sizi powder hot compress group or the conventional therapy group through a stratified randomization system, and acquire a random number (corresponding to the Yikou-Sizi powder hot compress and conventional therapy group or conventional therapy group) in this phase. The participants will be instructed to apply a Yikou-Sizi powder hot compress twice every day at 9:00 and 16:00 hours starting after the surgery (the day of surgery was excluded) until the time to defecation. The bowel sounds of the included subjects will be evaluated at least three times per day (1:00–9:00, 9:00–17:00, and 17:00–1:00) after surgery and were recorded in the case report form (CRF) until the time of patient release from the hospital. Patients will be called on the 14th day and the 120th day to inquire about and monitor any adverse events (Fig. 1).

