### Randomization

2.7

Participants that had undergone laparoscopic colorectal cancer surgery (n = 220) and laparoscopic total hysterectomy (n = 220) will be randomly assigned to the Yikou-Sizi powder hot compress and conventional therapy group or conventional therapy group. The randomized number will be generated by the network (http://www.gztcmgcp.com/sjxt/login.asp) and saved by statistical professionals.

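### Section 2.12 gives surgery type no role despite stratified allocation, and its pair-wise step does not fit two arms, so the treatment comparison is not defined

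*Protocol article*

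**What the plan says.** Four sections of the protocol article bear on this.

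- **Section 2.5, Trial procedure.** Patients go to the hot compress group or the "conventional therapy group through a stratified randomization system". The stratification factor is not named.
- **Section 2.7, Randomization.** Enrolment is fixed by operation: "laparoscopic colorectal cancer surgery (n = 220) and laparoscopic total hysterectomy (n = 220)". Each patient receives either compress plus conventional therapy or conventional therapy alone, so there are two arms.
- **Section 2.11, Sample size estimation.** The formula is "based on completely random design sample mean comparison". It ends at 110 per group, from which the section derives 220 patients for each operation.
- **Section 2.12, Data collection and statistical analysis methods.** For continuous data: "Comparison among groups will be analyzed by analysis of variance (ANOVA) and pair-wise comparison". If variances are unequal or the distribution is not normal, a rank-sum test with pair-wise comparison is used. For counts: "chi-square test at an α = 0.05 given a 2-sided test". No factor, stratum or separate analysis by operation is mentioned.

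**The concern.** The method in section 2.12 does not match the design in sections 2.5 and 2.7. A follow-up pair-wise comparison belongs to an analysis of three or more groups, and this trial has two arms. The phrase has content only if the groups are the four surgery-by-arm cells, and then most of the pairs are not randomized comparisons.

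The section therefore leaves at least three treatment tests open: the two arms pooled over 440 patients, separate tests within each 220, or a four-cell analysis. They answer different questions and have different power, and the text does not prevent a choice after the data are seen. If the pooled test is meant and surgery type is left out, any mean difference between the operations enters the residual variance.

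**Working it through.** **Inputs from section 2.11.** "where α = 0.05 and β = 0.2, given a 2-sided test". Time to first flatus: "1 = 75.47 hours, S1 = 39.44" and "2 = 64.29 hours, S2 = 24.96". Time to bowel sounds: 44.13 h (SD 32.58) and 31.22 h (SD 24.26). Dropout is 15%.

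**The plan's own figure.** n per group = 2(1.960 + 0.842)² σ²/δ². For bowel sounds, δ = 44.13 − 31.22 = 12.91 and the average SD is (32.58 + 24.26)/2 = 28.42, which gives n = 77, the stated number. So 77 is a simple two-group calculation without strata.

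**The possible pairs.** Two arms give 1 pair. Four cells give 4 × 3/2 = 6 pairs. Two of these compare the arms within one operation; the other 4 compare different operations.

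**Power under the readings left open.** For flatus δ = 75.47 − 64.29 = 11.18 and σ = √[(39.44² + 24.96²)/2] = √1089 = 33.00. For bowel sounds δ = 12.91 and σ = 28.72, by the same formula. Power = Φ(δ/(σ√(2/n)) − z), with full enrolment and before dropout:

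| Reading | Flatus | Bowel sounds |
|---|---|---|
| Pooled, adjusted for surgery type, 220 per arm | 94.4% | 99.7% |
| Separate by operation, 110 per arm, each at 0.05 | 71.0% | 91.5% |
| Separate by operation, each at 0.025 | 60.7% | 86.3% |
| Four cells, overall 3-df F test (operations assumed equal) | 85.6% | 98.5% |
| Four cells, one within-operation pair at 0.05/6 | 45.0% | 75.6% |

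All six pairs tested at 0.05 without correction carry a family-wise error of about 20% when no cells differ.

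**Pooled test without surgery type.** Let D be the difference in mean recovery time between the operations. The article does not give D, so the values below are assumptions. With equal strata the unadjusted variance is 1089 + D²/4, and the standard error grows by R = √(1 + D²/(4 × 1089)). Under stratified allocation, true alpha = 2[1 − Φ(1.96 R)] and power = Φ(δ/SE − 1.96 R), where SE is the adjusted standard error. After dropout there are 220 × 0.85 = 187 per arm, so SE = 33.00 × √(2/187) = 3.413 and δ/SE = 11.18/3.413 = 3.275.

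| D (assumed) | R | True alpha | Power for flatus |
|---|---|---|---|
| 0 h | 1.000 | 5.0% | 90.6% |
| 12 h | 1.016 | 4.6% | 90.0% |
| 20 h | 1.045 | 4.1% | 89.0% |
| 40 h | 1.169 | 2.2% | 83.7% |

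The adjusted test has 90.6% power throughout. The calculation takes 1089 as the variance within one operation. The article does not say which operations the preliminary data came from. If they were mixed, 1089 already contains some of D²/4 and the figures would change, though not the direction.

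**The case against.** The strongest objection is that a journal article condenses its methods, and that model factors and covariate adjustment are commonly left to an analysis plan that is not shown here. That is right as far as it goes: the absence of an adjustment is not in itself an error. What remains is that section 2.12 does state a method, and its pair-wise step does not fit the stated two arms.

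Several stronger readings are tempting, and the document does not support them:

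- A reader might infer a one-way ANOVA that deliberately ignores surgery type. The text says only ANOVA and names no factors.
- A reader might take "based on completely random design sample mean comparison" as the analysis model. It describes the sample size formula only.
- A reader might conclude that confidence intervals will be too wide. That requires both a pooled two-arm test without surgery type and a real difference between the operations. The article states neither. In separate or four-cell analyses, surgery type is already out of the error term.
- A reader might fear false positives from the pooled test. Omitting the stratum makes that test conservative.
- A reader might treat surgery type as the documented stratum. It is a strong inference from the fixed 220 and 220, but the factor is not named.

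The step in section 2.11 from 110 per group to 220 per operation may also mean that two parallel comparisons were intended. That reading is reasonable, but section 2.12 does not declare it or say how alpha would be handled.

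**Conclusion.** The point holds as a mismatch between design and analysis text. The pair-wise step is empty for two arms and mostly non-randomized for four cells, and the treatment test is not fixed. The main consequence is the choice left open: on section 2.11's own inputs, flatus power is 94.4% for the pooled adjusted test and 71.0% for each separate test before dropout.

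The efficiency loss from pooling without surgery type is secondary and conditional. It is nil if the operations recover alike, about 0.6 percentage points of power at 12 h and about 7 points at 40 h, and power stays above the planned 80% throughout that range. These figures assume equal strata, 187 per arm, normal approximations and a within-operation variance of 1089. The point is worth correcting, but it does not by itself threaten the validity of the trial.

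**What to change.** In section 2.12, replace the ANOVA and rank-sum sentence with one primary contrast of the two randomized arms, with surgery type as a factor or stratum:

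- continuous outcomes: a linear model with treatment and surgery type, or the van Elteren test if the distribution is not normal;
- counts: the Cochran-Mantel-Haenszel test stratified by surgery type.

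Report estimates for each operation and the treatment-by-surgery interaction descriptively. Delete the pair-wise step. Name the stratification factor in section 2.5 or 2.7.

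If the sponsor intends two separate per-operation comparisons, declare that instead, with the alpha for each. This is a different question from the pooled effect, and it has the lower power shown above, so the choice should be deliberate and made before the data are seen.

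The cost is wording only. Surgery type is known for every patient, and no new data or patients are needed.

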## Introduction

1

Postoperative gastrointestinal dysfunction (PGD) is a common postoperative complication of patients undergoing surgery.^[1–8]^ PGD is caused by surgical trauma, anesthesia, electrolyte disturbance, abdominal cavity inflammation, residual hemorrhage, or drainage tube mechanical stimulation.^[8–10]^ It is characterized by a series of symptoms such as nausea, vomiting, flatulence, defecation difficulty, abdominal distension, and abdominal pain, which are regarded as inevitable reactions after anesthesia and surgery.^[11]^ One of the worst complications is delayed resumption of gastrointestinal function, known as postoperative ileus (POI).^[12]^ This can prolong hospital stays, raise healthcare costs, and increase morbidity and mortality.^[9,13,14]^ POI usually resolves within approximately 3 days, although it can last longer in some cases as a condition termed postoperative paralytic ileus.^[15,16]^ Postoperative use of opioid-based analgesics can increase the incidence of POI.^[17,18]^ The treatment for the recovery of gastrointestinal function mainly focuses on rehydration, oxygen supply, electrolytes, acid–base imbalance, infection prevention, spasticity and pain relief, gastrointestinal decompression, prokinetic drug usage, and related hormonal intervention.^[19]^

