### Inclusion criteria

2.2

The inclusion criteria are as follows:

1)Underwent laparoscopic colorectal cancer surgery and laparoscopic total hysterectomy2)Age from 40 to 75 years old3)Anesthesia time was within 1.5 to 4.5 hours4)Duration of surgery was 1 to 4 hours5)The TCM syndrome was identified as Qi stagnation syndrome6)Willing to sign an informed consent document

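### The primary recovery times are compared by group alone, although operation type, age and duration of surgery are known before treatment; a prespecified adjusted model would be modestly more precise.

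*Protocol article*

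**What the plan says.** Section 2.9 (Endpoints) defines the main outcomes as times: "Primary endpoints are as follows: time to first flatus, time to first defecation, time to first bowel sounds", together with time to starting diet.

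Section 2.12 (Data collection and statistical analysis methods) gives the rule for such data: "Comparison among groups will be analyzed by analysis of variance (ANOVA) and pair-wise comparison". Where variances differ or the distribution is not normal, "heteroscedasticity data or abnormal distribution will be analyzed by the rank-sum test and pair-wise comparison". Neither sentence names a covariate, a stratum or a model.

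Elsewhere the article shows what is known about each patient before treatment:

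- Section 2.2 (Inclusion criteria): "Age from 40 to 75 years old", "Anesthesia time was within 1.5 to 4.5 hours" and "Duration of surgery was 1 to 4 hours". All three must be recorded to apply the criteria.
- Sections 2.7 and 2.11: 220 patients for each of two operations, laparoscopic colorectal cancer surgery and laparoscopic total hysterectomy.
- Section 2.5 (Trial procedure): allocation goes through a stratified system, whose strata are not named. The compress starts after surgery, not counting the day of surgery.

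The Introduction gives the prognostic reason: "PGD is caused by surgical trauma, anesthesia, electrolyte disturbance, abdominal cavity inflammation", among other factors.

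**The concern.** A group-only comparison leaves in the error term any variation in recovery time that comes from the operation itself. The protocol's own account of the condition points to surgical trauma and anesthesia, and duration of surgery is a recorded measure of that exposure. Operation type separates two different populations that are enrolled in equal numbers. Age is recorded too, although the Introduction does not name it as a cause.

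If these variables predict recovery time, confidence intervals will be wider than they need to be for the same patients. What is at stake is precision. If no adjusted model is fixed in advance, any adjustment added later could also be questioned as chosen after seeing results.

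**Working it through.** **Inputs (section 2.11).** Two-sided α = 0.05, power 80%. Flatus: means 75.47 and 64.29 h, SDs 39.44 and 24.96. Bowel sounds: means 44.13 and 31.22 h, SDs 32.58 and 24.26. Stated result: 77 per group before dropout. Planned: 110 per group within each operation, hence 220 per arm if the operations are pooled. Dropout 15%.

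**Step 1: the plan's own figure.** n per group = 2(1.960 + 0.842)² SD² / d².

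- Bowel sounds: d = 44.13 − 31.22 = 12.91. With SD = √((32.58² + 24.26²)/2) = 28.72, n = 78. With the simple average SD of 28.42, n = 77. The stated 77 is reproduced as an unadjusted comparison of two means.
- Flatus: d = 75.47 − 64.29 = 11.18, SD = √((39.44² + 24.96²)/2) = 33.0, n = 137.

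**Step 2: effect of adjustment.** In a linear ANCOVA on hours, the residual SD is SD × √(1 − R²). The documents give no R², so 5%, 10% and 20% are assumptions. Power = Φ(d / (SD √(1 − R²) √(2/n)) − 1.960).

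Worked case, flatus, n = 110, R² = 0: standard error = 33.0 × √(2/110) = 4.45 h; 11.18/4.45 = 2.51; Φ(2.51 − 1.96) = 0.71.

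| Flatus power | R² = 0 | 0.05 | 0.10 | 0.20 |
|---|---|---|---|---|
| One operation, 110 per group | 71% | 73% | 75% | 80% |
| One operation, 93 per group (after 15% dropout) | 64% | 66% | 68% | 73% |
| Pooled, 220 per arm | 94% | 95% | 96% | 98% |
| Pooled, 187 per arm (after 15% dropout) | 91% | 92% | 93% | 96% |

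Bowel sounds at 110 per group: 91% unadjusted, 93% to 96% for R² of 5% to 20%.

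**Step 3: the same gain as interval width.** The 95% half-width for flatus within one operation is 1.96 × 4.45 = 8.7 h unadjusted. It becomes 8.5 h at R² = 0.05 (× √0.95 = 0.975) and 7.8 h at R² = 0.20 (× √0.80 = 0.894). Intervals are therefore about 2.5% to 10.6% narrower. In sample-size terms the gain is 1/(1 − R²), from 1/0.95 = 1.05 to 1/0.80 = 1.25.

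**Step 4: which row goes with which model.** Within one operation, operation type is constant and cannot be a covariate, so the 110-per-group rows describe a model with age and duration only. A model that includes operation type requires pooling, so the 220-per-arm rows apply. The pooled rows assume the same difference and SD in both operations. The article does not say whether the operations will be pooled.

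**Step 5: are the covariates pre-treatment?** Section 2.7 describes participants as already operated on when randomized; section 2.5 is less clear about the moment of allocation. On either reading, duration of surgery is fixed before the first compress, so the compress cannot affect it.

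**The case against.** The strongest reply is that nothing here is wrong. Under randomization a two-group comparison needs no covariates to be valid. Section 2.12 is a general rule in a condensed article, and an analysis plan that is not shown could name covariates. The first part stands in full. The second stands in part: the article states its comparison method explicitly and the method is group-only, but it does not rule out an adjusted model elsewhere.

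Four further objections also hold and limit the point:

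- R² is assumed. The eligibility limits on age, anesthesia time, surgery time and blood loss narrow the patient mix, so R² may be low. At 5% the gain within one operation is about two percentage points. The 1-to-4-hour range is what is permitted, not a spread that has been observed.
- A reader might infer that adjustment cures the flatus sample size, which needs 137 per group against a stated 77. The documents do not support this. Within one operation, 80% is reached only at R² = 20% and before dropout; pooled, there is no shortfall on these inputs. The derivation in section 2.11 is a separate matter.
- A reader might carry the 1/(1 − R²) gain over to a Cox model. It does not apply there: adjustment changes the hazard ratio being estimated rather than shrinking a residual variance. For a log-time model the direction should be the same, but the article gives no log-scale SD from which to compute the size.
- The pilot SDs for flatus differ (39.44 against 24.96), which could trigger the rank-sum fallback. The power figures do not model that.

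**Conclusion.** The point holds as a modest gain in precision that needs no new data. The planned comparison is valid; a reader might take its lack of covariates for bias or for an error, and the documents support neither. For an assumed R² of 5% to 20% on the hours scale, flatus power at full enrolment rises by about 2 to 9 percentage points within one operation and by about 1 to 4 if the operations are pooled. Both rest on the pilot means and SDs in section 2.11, a common SD of 33.0 and a normal approximation. The benefit matters more if each operation is analysed separately. Confidence is high that the stated analysis uses no covariate and that the covariates are available, and low on the size of R².

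**What to change.** In section 2.12, prespecify one primary model for the recovery times:

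- A linear ANCOVA with group, age and duration of surgery. Add operation type if the two operations are pooled; omit it if each is analysed separately. State which of the two applies.
- Use log time if the times are skewed, and fix the rule for that choice before group labels are seen. Skew is plausible: the pilot SDs for bowel sounds are 32.58/44.13 = 74% and 24.26/31.22 = 78% of their means.
- Keep the unadjusted ANOVA or rank-sum test as a sensitivity analysis.
- Do not adjust for anything that arises after the start of treatment.

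The cost is a change of wording and slightly more analysis work. No new data, patients or visits are needed.
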